## Abstract

**Background:**

Glioblastoma is the most frequent and malignant primary brain tumor. Even in the subgroup with O-6-methylguanine-DNA methyltransferase (MGMT) promoter methylation and favorable response to first-line therapy, survival after relapse is short (12 months). Standard therapy for recurrent MGMT-methylated glioblastoma is not standardized and may consist of re-resection, re-irradiation, and chemotherapy with temozolomide (TMZ), lomustine (CCNU), or a combination thereof. Preclinical results show that meclofenamate (MFA), originally developed as a nonsteroidal anti-inflammatory drug (NSAID) and registered in the USA, sensitizes glioblastoma cells to temozolomide-induced toxicity via inhibition of gap junction-mediated intercellular cytosolic traffic and demolishment of tumor microtube (TM)-based network morphology.

**Methods:**

In this study, combined MFA/TMZ therapy will be administered (orally) in patients with first relapse of MGMT-methylated glioblastoma. A phase I component (6–12 patients, 2 dose levels of MFA + standard dose TMZ) evaluates safety and feasibility and determines the dose for the randomized phase II component (2 × 30 patients) with progression-free survival as the primary endpoint.

**Discussion:**

This study is set up to assess toxicity and first indications of efficacy of MFA repurposed in the setting of a very difficult-to-treat recurrent tumor. The trial is a logical next step after the identification of the role of resistance-providing TMs in glioblastoma, and results will be crucial for further trials targeting TMs. In case of favorable results, MFA may constitute the first clinically feasible TM-targeted drug and therefore might bridge the idea of a TM-targeted therapeutic approach from basic insights into clinical reality.

**Trial registration:**

EudraCT 2021-000708-39. Registered on 08 February 2021

## Administrative information

Note: the numbers in curly brackets in this protocol refer to SPIRIT checklist item numbers. The order of the items has been modified to group similar items (see http://www.equator-network.org/reporting-guidelines/spirit-2013-statement-defining-standard-protocol-items-for-clinical-trials/).

## Introduction

### Background and rationale {6a}

Glioblastoma is known as the most frequent (3000 new cases/year in Germany) and most malignant (median overall survival (mOS) 17 months) primary brain tumor in adults [1, 2]. The subgroup of patients with a methylation of the MGMT promotor (approximately 1/3 of patients) exhibit a better clinical responding to alkylating chemotherapy with temozolomide (TMZ) or lomustine (CCNU) and thus have a longer mOS (26–48 months) than the subgroup of patients with non-methylated MGMT promotor. Nevertheless, recurrence occurs after a median period of roughly 16 months [3]. Here, a re-exposure to alkylating therapy is commonly applied, but the outcome is dismal with a median progression-free survival (mPFS) time of about 3 months and a mOS of 10–12 months after relapse [4, 5]. Thus, there is an urgent medical need for improved therapies for recurrent glioblastoma.

Previous preclinical studies have shown that glioblastoma cells exhibit ultra-long and thin membrane protrusions—dubbed tumor microtubes (TMs)—that extend into the surrounding (healthy) brain and tumor tissue in order to interconnect tumor cells over long distances [6]. TMs also interact with neurons through AMPAergic synapses which integrate the tumor cells into neural circuits and foster the malignant growth of these tumors by synaptic activity [7, 8]. The intercellular contacts are established by the aid of connexin-43 (Cx43)-based gap junctions that ultimately enable glioblastoma cells to arrange a multicellular functional network. Functional TMs, in turn, are associated with resistance to cytotoxic treatment through the formation of a self-repairing syncytial network which can be efficiently disturbed by downregulation of Cx43. Once the ability to establish TM networks is compromised, both TMZ chemotherapy and radiotherapy become much more efficient in preclinical glioblastoma models [6, 9].

In line with this, several studies demonstrated that pharmacological inhibition of gap junctions sensitizes primary MGMT-methylated human glioblastoma cell populations to TMZ-mediated toxicity [10–13].

However, a direct transfer into the clinical application has not been feasible so far, since none of the previously discussed gap junction inhibitors is suitable and available for clinical application.

Meclofenamate (MFA)—a nonsteroidal anti-inflammatory drug (NSAID) with clinical use in the USA—has been shown to exert distinct gap junction-inhibitory effects in various physiological cell types [14–16]. In addition, the formation of tumor-promoting glioblastoma-neuron synapses is inhibited by MFA [8]. Based on this knowledge, in our very recently published work [17], we aimed to investigate to what extent MFA might affect gap junction-mediated intercellular cytosolic traffic as well as electrical coupling in preformed glioblastoma networks. Our results show MFA to lead to both a morphological and a functional breakdown within glioblastoma network arrangements. This breakdown is driven by MFA-mediated inhibition of TM outgrowth and intercellular communication via two mechanisms: (1) a direct connexin-43 inhibition leading to significantly reduced intercellular gap junction-mediated cytosolic traffic and (2) a downregulation of adhesion and axon guidance molecules that spawns a reduction in the length of TMs leading to morphologically isolated tumor cells within the malignant network. This functional and morphological breakdown of glioblastoma intercellular networking resulted in a profound sensitivity to TMZ-mediated antitumor effects.

To summarize, preclinical results provide evidence for MFA to constitute the first potential TM-targeted drug that—with regard to its clinical approval as a NSAID in the USA—might be suitable for a clinical use. Based on this, the MecMeth/NOA-24 trial now explores the toxicity of a combination of MFA and standard TMZ, establishes a tolerable dose of MFA in this combination therapy in patients with relapsed MGMT-methylated glioblastoma (phase I), and ultimately searches for first signs of efficacy of this combination (phase II).

### Objectives {7}

In the phase I component, the primary objective is to determine the toxicity of MFA therapy in addition to standard TMZ and, on this base, to determine the daily MFA dose to be applied in a phase II component. Efficacy, safety, tolerability, and clinical effect on the quality of life of MFA in addition to standard TMZ throughout the trial constitute the secondary objectives.

In phase II, the main objective is to determine the efficacy of MFA therapy in addition to standard TMZ therapy. For this purpose, the dose determined in phase I will be used. Besides that, safety, tolerability, and clinical effect on the quality of life of MFA therapy in addition to standard TMZ will be investigated.

### Trial design {8}

The study consists of a single-arm phase I part and a randomized, parallel-group, and unblinded phase II part.

In phase I, patients with the first relapse of MGMT-methylated glioblastoma are screened for the trial. After inclusion, patients are pretreated with MFA in addition to standard TMZ and tumor resection will be performed 7–10 days after initiation of therapy. MFA tissue level measurements and translational analyses are performed on the tumor material obtained from resection. Each patient is particularly screened for dose-limiting toxicities (DLTs) during the first 8 weeks of his/her MFA treatment. Patients are recruited in two cohorts of three to six patients. Dose adaptation in between cohorts depends on the occurrence of DLTs as described below.

All patients of phase I are followed for toxicity and efficacy until the end of phase II.

In phase II, patients with the first relapse of MGMT-methylated glioblastoma are screened for the trial. After inclusion, patients are randomized (1:1) into two parallel groups, the experimental or the standard treatment arm. The experimental treatment is defined as treatment with MFA (dose determined in phase I) in addition to standard TMZ. The standard treatment arm is defined as monotherapy with TMZ (150–200 mg/m^2^ body surface). If tumor resection for the relapsed tumor is clinically indicated, the local treating neurosurgeon can decide whether the resection can be safely postponed until day 7–10 after initiation of therapy (optional, not a prerequisite for study participation in phase II) and tumor material for determination of MFA levels can be obtained.

MFA is taken at the dose determined in phase I. Daily MFA treatment is continued for 8 4-week courses (i.e., 224 days), until tumor progression, until the occurrence of a DLT attributable to MFA, or until definitive discontinuation of standard TMZ, whatever comes first. In case MFA therapy is terminated, standard TMZ therapy can be continued at the discretion of the treating physician.

## Methods: participants, interventions, and outcomes

### Study setting {9}

Phase I of the trial will be conducted in 10 centers in Germany (all academic hospitals), which must meet the structural and personnel requirements for performing the planned regular trial-related investigations. In phase II, the trial will be conducted in the 10 centers of phase I plus five additional German centers (all academic hospitals).

### Eligibility criteria {10}

Inclusion criteria for participants (phase I and II):
First relapse after first-line therapy with radiotherapy (RT) and alkylating chemotherapy, > 3 months after last chemotherapy application, and > 6 months after the end of RT. Drug therapy and/or radiotherapy for first relapse treatment not yet startedTumor progression according to response assessment in neurooncology (RANO) criteriaWritten informed consentCognitive state to understand rationale and necessity of study therapy and proceduresMGMT promotor-methylated, isocitrate-dehydrogenase (IDH) wildtype glioblastoma or gliosarcoma confirmed with histology of the primary resectionAge > 18 yearsKarnofsky Performance Score (KPS) ≥ 60%Life expectancy > 6 monthsAdequate bone marrow reserve (white blood cell count (WBC) > 3 G/nl, platelets > 100 G/nl)Adequate liver function (bilirubin < 1.5 × upper limit of normal (ULN); ASAT/ALAT < 3 × ULN, creatinine < 1.5 × ULN)Patient compliance and geographic proximity that allow adequate follow-upMale and female patients with reproductive potential must use an approved contraceptive method during and for 3 months after the trial (Pearl index < 1%)Pre-menopausal female patients with childbearing potential: a negative serum pregnancy test (beta-HCG) must be obtained prior to treatment start

*Additional criterion for phase I:*

## Resection at first relapse not yet performed; according to the local treating neurosurgeon and the documented decision of local neurooncological tumor board, re-resection of the tumor is clinically indicated and can be safely deferred until day 7–10 after initiation of MFA/TMZ therapy

Exclusion criteria for participants (phase I and II):
Indication for hematotoxicity in first-line therapy not allowing TMZ starting dose 150 mg/m^2^/daySkin or liver toxicity > Common Terminology Criteria of Adverse Events (CTCAE) 5 grade 1 in first-line therapyHistory of gastrointestinal (GI) bleeding or gastroduodenal ulcer, active gastritisHistory of asthma, urticaria, or allergic-type skin reactions to NSAIDPrior malignancy other than gliomaHistory of confirmed or suspected hypersensitivity (delayed type and immediate type, inclusive of anaphylactic reaction) to any background/standard TMZ drug product or one of its ingredients of the chosen product, or to cyclooxygenase inhibitors (“NSAIDs”), or to any ingredient of meclofenamate drug productHistory of disease with poor prognosisSevere coronary heart disease (esp. after coronary artery bypass graft or history of myocardial infarction), severe heart failureKnown HIV infection, active hepatitis B or CBreastfeeding or pregnantUnable to undergo contrast-enhanced magnetic resonance imaging (MRI) (i.e., contrast allergy, implants, etc.).Treatment in another clinical trial with therapeutic medical intervention or use of any other investigational agent during the trial or within the 30 days before enrolmentMedication with a drug that is not allowed in conjunction with MFA intake and cannot be discontinued, i.e., lithium, methotrexate, etc.Patients with active bleeding, bleeding diathesis, antiplatelet therapy, or anticoagulant therapy except for the following anticoagulants which are permitted for low-dose thrombosis prophylaxis up to the dosage specified here: unfractionated heparin 7500 IU BID or 5000 IU TID; low molecular weight heparin, e.g., enoxaparin 40 mg/day; fondaparinux 2.5 mg/day; danaparoid sodium 750 IU BID; argatroban IV route thrombin time < 70 s; vitamin-K-antagonist INR < 1.8; dabigatran 150 mg BID; rivaroxaban 10 mg/day; edoxaban 30 mg/day; and epixaban 2.5 mg BID. This restriction is due to a potentially increased risk of GI ulcers with subsequent bleeding under MFA therapy.Patients with medically diagnosed hereditary galactose intolerance, complete lactase deficiency, or confirmed glucose-galactose malabsortionMedical history of gastrointestinal resection of any kind that may potentially alter the absorption of the investigational study drug, according to investigators’ judgmentThe presence of any other concomitant severe, progressive, or uncontrolled renal, hepatic, hematological, endocrine, pulmonary, cardiac (including coronary artery bypass graft), or psychiatric disease, or signs and symptoms thereof, that may affect the subject’s participation in the study, according to investigators’ judgment

### Who will take informed consent? {26a}

Informed consent will be obtained by the investigator (a physician experienced for a minimum of 2 years in the care of brain tumor patients) of the respective center. The patient will receive an informed consent sheet where study rationale, design, risks, and potential benefits are precisely described. Additionally, there will be a detailed explanatory meeting with the investigator where this information will be explained and where the potential participant will have enough time to ask questions. Thereafter and after having read the informed consent sheet, the patient can give written informed consent. An adequate consideration time of 24 h will be given.

### Additional consent provisions for collection and use of participant data and biological specimens {26b}

Information on the collection and use of participant data and biological material (e.g., blood, tumor tissue) will be covered by a separate informed consent sheet.

## Interventions

### Explanation for the choice of comparators {6b}

In the treatment of relapsed MGMT promotor-methylated glioblastoma, standard chemotherapy may consist of TMZ or CCNU. Patients who relapse after a therapy-free time interval following the completion of first-line TMZ therapy may have a chance to respond again to TMZ therapy [5]; thus, TMZ therapy is justified as standard therapy in the standard arm.

### Intervention description {11a}

In phase I, there is one treatment arm and a dose-finding algorithm will be performed as described in the following. The participants will receive standard TMZ therapy for eight cycles (TMZ application orally on day 1–5 in a 28-day cycle, dose 150–200 mg/m^2^ body surface). In addition to that, the first three patients will receive 2 × 100 mg/day MFA daily (see also Fig. 1 dose-finding scheme). If no DLT occurs, the next three patients will be treated with 2 × 200 mg/day. Again, if no DLT occurs, this dose will be used for phase II. In both steps, if 1/3 patients develop a DLT, another three patients will be included. If there is a DLT in 1/6 patients, the dose will be elevated or the 2 × 200 mg/day dose will be used for phase II. If > 1 DLTs occur, the dose will be reduced in a next step to 2 × 50 mg/day and the same algorithm will be applied. If there are > 1 DLTs in 6 patients and the lowest dose of 2 × 50 mg/day, phase II will not be initialized. DLT is determined in the first 2 courses of MFA (within 8 weeks/56 (±3) days after first study treatment administration) in subjects with a compliance rate of 90% (i.e., 50 days of treatment) and no overdose. If judged to be related to the administration of MFA, the following toxicities will be considered a DLT: grade ≥ 4 hematotoxicity for > 14 days in courses 1 and 2; grade ≥ 3 for any other organ toxicity.

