### Sample size {14}

Phase I uses an adaptive design based on DLTs (see Fig. 1). Starting with 3(-6) patients per dose level is standard for dose finding in phase I. Starting with a middle-level MFA dose of 2 × 100 mg/day (according to the US registration of MFA) ensures that only two dose levels have to be explored (*n* = 6–12 patients). Patients not evaluable for DLT or MFA tumor levels will be replaced (conservative estimate, 1/6 patients; thus maximal patient number in phase I, 12 + 2 = 14).

The randomized phase II part accrues 30 patients per arm. For the evaluation of PFS, the experimental arm also includes the 3–6 patients of phase I which have been treated with the same dose of MFA as in phase II for an additional analysis. Since phase II is searching for indications of efficacy but is not a confirmatory trial, dropouts will not be replaced. In glioblastoma trials, the dropout rate is relatively low (e.g., 9% in CeTeG/NOA-09 trial). Therefore, and since data from dropout patients are included as censored observation, the results may be expected to be robust regarding patients with short follow-up/early dropouts.

With 30 subjects per arm and a two-sided alpha level of 10%, we could detect a hazard ratio of approximately 0.44 if we assume a PFS-6 of 40% for the reference treatment and use a power of 80%.

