### Methods in analysis to handle protocol non-adherence and any statistical methods to handle missing data {20c}

In phase I, patients who are not evaluable for DLT will be replaced. A patient is evaluable for DLT if the DMSB has determined that a DLT has occurred in this patient during the first 56 days after treatment start (independent of the duration of MFA intake) or if until DLT visit (day 56 ± 3 days after start of MFA treatment) the patient has taken at least 100 doses of MFA (i.e., 89.3% of the maximally positive cumulative dose in 56 days) as documented by the patient’s diary and the documented return of 1 empty container of MFA (containing 100 capsules) (for dose step 2 × 100 mg daily or 2 × 50 mg daily) or of 2 empty containers of MFA (for dose step 2 × 200 mg daily).

In phase II, subjects dropping out of the trial prior to randomization will be listed as screening failures including the reason for dropout. Subjects prematurely discontinuing the trial will be censored regarding the analysis of PFS or OS at the time of discontinuation. Subjects dropping out after randomization will be analyzed using all available data and will not be replaced. The technique for the analysis of missing values will be defined in the statistical analysis plan. A check of a possible treatment effect on the frequency of missing values will be performed.

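### Two sections give conflicting rules for which phase I patients count towards DLT: one requires about 50 days of MFA even of a patient whom a DLT stopped, the other does not

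*Protocol article*

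**What the plan says.** Four parts of the protocol article bear on who enters the DLT count.

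- **Intervention description {11a}**, which sets out the dose-finding algorithm, determines DLTs over the first two MFA courses, "within 8 weeks/56 (±3) days after first study treatment administration", and "in subjects with a compliance rate of 90" percent, given as 50 days of treatment, without overdose. It has no exception for a patient who has already had a DLT.
- **Non-adherence and missing data {20c}** gives two routes to being evaluable. A patient qualifies if the DSMB finds a DLT "during the first 56 days after treatment start (independent of the duration of MFA intake"). Otherwise, "the patient has taken at least 100 doses of MFA (i.e., 89.3% of the maximally positive cumulative dose in 56 days") by the DLT visit. Patients who meet neither route are replaced. Overdose is not mentioned.
- **Criteria for discontinuing {11b}** end MFA for MFA-related grade 3 or higher organ toxicity, except asymptomatic grade 3 laboratory changes, and for MFA-related grade 4 hematotoxicity lasting more than 14 days in courses 1 and 2.
- **Replacement** is also mentioned in two other places. Sample size {14} says: "Patients not evaluable for DLT or MFA tumor levels will be replaced". Statistical methods {20a} replaces early dropouts and patients with insufficient 8-week DLT data. Neither says what happens to a DLT already observed in such a patient.

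**The concern.** A DLT is itself a reason to stop the drug. If the DLT count is limited to patients who completed about 50 days of MFA, early toxicity removes a patient from the set in which toxicity is counted. Because {11a} expresses compliance as 50 days of treatment, it cannot easily be read as adherence while on drug. The rule in {20c} avoids the problem by making a DLT sufficient on its own. Both rules are stated in the same article and cannot both govern one count.

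The count decides escalation, the phase II dose and whether phase II starts. Under {21a} the DSMB meets on a dose step once all its patients are evaluable for DLT, so the definition of evaluable also determines which patients the board reviews.

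**Working it through.** **1. The plan's own threshold.** Two doses a day for 56 days is 112 doses. 100/112 = 0.893 and 50/56 = 0.893, so the 89.3% in {20c} reproduces. The 50 days in {11a} is the same threshold, rounded there to 90% (0.90 × 56 = 50.4 days).

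**2. The two rules side by side.**

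| Phase I patient | {11a} as worded | {20c} |
|---|---|---|
| No DLT, at least 50 days / 100 doses | counted | counted |
| No DLT, less exposure | not counted | replaced |
| DLT, MFA stopped before about day 50 | not counted | counted |
| DLT after about day 50, or one that does not stop MFA, with the threshold met | counted | counted |

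The overdose condition aside, the rules differ only in the third row.

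**3. Effect on dose finding if {11a} governed.** Under {11a} a dose level is accepted with 0 DLTs in 3 patients, or with 1 in 3 followed by 0 in the next 3:

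P(accept) = (1−p)³ + 3p(1−p)² × (1−p)³ = (1−p)³ + 3p(1−p)⁵

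If a share q of DLT patients is replaced, and replacement continues until the cohort is full, the DLT risk among counted patients is

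p′ = p(1−q) / (1−pq)

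The article gives neither p nor q; both are assumptions. Three values of q span the range:

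- q = 0: every DLT counts, as in {20c}.
- q = 0.5: half of the DLT patients are replaced.
- q = 50/56 = 0.893: onset is uniform over 56 days and every DLT stops MFA.

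For p = 0.33:

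- q = 0: 0.67³ + 3 × 0.33 × 0.67⁵ = 0.301 + 0.134 = 0.434.
- q = 0.5: p′ = 0.165/0.835 = 0.198; P = 0.714.
- q = 50/56: p′ = 0.0354/0.7054 = 0.050; P = 0.857 + 0.116 = 0.973.

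The same formulas for other assumed risks:

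| p | q = 0 | q = 0.5 | q = 50/56 |
|---|---|---|---|
| 0.20 | 0.71 | 0.89 | 0.99 |
| 0.33 | 0.43 | 0.71 | 0.97 |
| 0.40 | 0.31 | 0.60 | 0.95 |
| 0.50 | 0.17 | 0.43 | 0.91 |

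Taking 49/56 for onset strictly before day 50 gives 0.965 at p = 0.33, so the day convention hardly matters.

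**4. Tumor-level replacement.** Resection is on day 7–10. Under uniform onset, 6/56 to 9/56, or 11% to 16%, of DLTs would come before it and could leave the patient without a tumor level.

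**The case against.** The strongest reply is that {20c} already settles the matter. It is the only section that defines evaluability, with doses, diary and containers, and it explicitly protects patients with a DLT. Other sections agree with it: Outcomes {12} sets no compliance condition on DLT incidence, Trial design {8} screens each patient, and Interim analyses {21b} reports any DLT to the DSMB. On this view the sentence in {11a} is only a compressed form of the second route in {20c}. Much of this stands. A reader might infer from {11a} that the trial will discard its early DLTs and pass unsafe doses; the documents do not show that. What remains is that {11a}, the section containing the algorithm, states the restrictive rule without the exception or a cross-reference.

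Four narrower objections also hold.

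- The 97% is a bound. {11b} exempts asymptomatic grade 3 laboratory changes from stopping MFA, so not every DLT need end treatment. Hematotoxicity must last more than 14 days to qualify, so uniform onset cannot hold for it.
- The clause in {8} that continues MFA "until the occurrence of a DLT attributable to MFA" sits in the phase II description. The link between a DLT and stopping MFA in phase I therefore rests on {11b}.
- A reader might infer from {14} that a patient without a tumor level also loses an observed DLT. {14} says only that such a patient is replaced, and {20c} would still count the DLT. This needs clarification but is not an error.
- A reader might see two thresholds in 90% and 89.3%. They are one threshold, rounded once.

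**Conclusion.** The contradiction is real and concerns the phase I primary endpoint: {11a} and {20c} disagree about a patient whose DLT ended MFA before about day 50. Its cost depends on which rule is followed. Under {20c} it is zero. Under {11a} as worded, at an assumed 33% risk, the probability of accepting a dose level rises by 28 percentage points (71 − 43) if half of the DLT patients are replaced, and by at most about 54 (97 − 43) under uniform onset with every DLT stopping MFA. These figures describe a literal reading of {11a} and are not a forecast of how the trial will run. DLTs after about day 50, and those that do not stop MFA, are not at risk. The sections should be reconciled before any cohort decision, because even the middle case weakens the dose-finding gate materially.

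**What to change.** Wording changes only:

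- Name {20c} as the sole definition of DLT-evaluable and refer to it from {11a}.
- In {11a}, limit the compliance condition to patients without a DLT. State in {20c} whether the overdose condition applies to them, since only {11a} mentions it.
- In {14} and {20a}, state that replacement for any reason, including early dropout or a missing tumor level, never removes an observed DLT from the count.

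No dose, escalation step or stopping criterion needs to change for this. The only practical cost is that the DLT denominator may be one or two patients larger than the set with tumor levels.
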